**Fig. 1 f0005:**
[figure not shown]
**Study flowchart.***Abbreviations*: EAAA: East Anglian Air Ambulance; OHCA: out-of-hospital cardiac arrest; SPEAR: specialist percutaneous emergency aortic resuscitation; SOP: standard operating procedure; RFA: right femoral artery; RFV: right femoral vein; ERICA-ARREST: The Emergency Resuscitative Endovascular Balloon Occlusion of the Aorta in Out-of-Hospital Cardiac Arrest study; REBOA: resuscitative endovascular balloon occlusion of the aorta; ETCO2: end-tidal CO2; RsO2: cerebral regional oxygen saturation; AoDBP: aortic diastolic blood pressure; CVP: central venous pressure; CPR: cardiopulmonary resuscitation; ROSC: return of spontaneous circulation.

Alongside standard ETCO2 and cerebral oximetry monitoring, the proximal and distal arterial pressures will be measured during balloon inflation. The REBOA operator will then inflate the balloon with saline until the distal arterial pressure waveform is lost. Once the balloon is inflated, the REBOA catheter will be secured to prevent migration or dislodgement. If ROSC is achieved without significant instability, the balloon will be gradually deflated by 0.5 ml every 30 s, guided by invasive physiology. Post resuscitation care will follow standard EAAA and Resuscitation Council UK guidelines.^38^ Resuscitation will be terminated if the patient remains in cardiac arrest following standard EAAA protocols; considering the clinical context, patient factors, point-of-care ultrasound findings and blood gas analysis if available.

### Timescale

The study will continue until 20 ERICA-ARREST patients have been enrolled, or 24 months have elapsed. The study will end following the death or hospital discharge of the final patient or after 90 days since the hospital admission date of the final trial patient.

### Data collection

A paper case report form (CRF) will be completed for each case by the trial clinician undertaking the procedure (supplementary appendix). Within 24 h of the procedure, a structured post-event debrief will be conducted in collaboration with the Chief Investigator (CI) to ensure compliance with the protocol and correct documentation. Additional data relating to patient demographics and outcomes will be retrieved from data collected as part of routine patient care and aftercare (Table 3).

**Table 3 t0015:** Data collected per patient for the ERICA-ARREST feasibility trial of prehospital Zone I (supra-coeliac) REBOA for refractory non-traumatic OHCA.

**Field**	**Data points collected**	**Source**
End-tidal CO2 (ETCO2)	Per 30 s intervals throughout	Zoll X-series
Aortic diastolic pressure (AoDBP)	Per 30 s intervals throughout	Zoll X-series
Central venous/femoral venous pressure if available	Per 30 s intervals throughout	Zoll X-series
Cerebral oximetry (rSO2)	Per 1 s interval throughout	Nonin co-pilot cerebral oximeter
Age (Years)		Patient record/clinical team
Sex		Patient record/clinical team
Weight (Estimated kg)		Patient record/clinical team
Timings (hh:mm)	Estimated time of arrest 999 call EEAST arrival Estimated CPR time Estimated time of 1st defibrillation HEMS dispatch HEMS arrival HEMS depart HEMS handover at hospital Sustained ROSC time PLE	Patient record/clinical team
Cardiac rhythm	On EEAST arrival (& Time or rhythm) On HEMS arrival	Patient record/clinical team
Witnessed arrest	Yes/No	Patient record/clinical team
Bystander CPR	Yes/No	Patient record/clinical team
Bystander defibrillation	Yes/No	Patient record/clinical team
Suspected aetiology	Cardiac – myocardial infarction Cardiac – arrhythmia Cardiac – heart failure Respiratory – pulmonary embolism Respiratory – other Other	Patient record/clinical team
Known comorbidities		Patient record/clinical team
Number of defibrillation shocks		Patient record/clinical team
Adrenaline administered	Yes/No Total cumulative dose given	Patient record/clinical team
Airway management	Supraglottic airway Endotracheal Tube	Patient record/clinical team
Ventilation strategy	Oxylog/Manual	Patient record/clinical team
Survival to discharge	Yes/No	Aftercare
Complications related to vascular access	e.g. Local haemorrhage, lower limb ischaemia, infection, aortic dissection, femoral vessel dissection, rupture or injury, surgical intervention/repair needed	Aftercare
In contact with Aftercare	Yes/No	Aftercare
Consent given	Yes/No	Trial team/Aftercare
Date of consent		Trial team/Aftercare
Survival to 30 days	Yes/No	Aftercare

*Abbreviations:* EEAST: East of England Ambulance Service NHS Trust; CPR: cardiopulmonary resuscitation; HEMS: Helicopter Emergency Medical Service; ROSC: return of spontaneous circulation; PLE: pronounced life extinct.

At EAAA, there is a dedicated team of Aftercare nurses and paramedics who routinely contact patients and families (including bereaved families), to ensure they are receiving the appropriate support following their incident. The Aftercare team are able to signpost individuals to the appropriate services for physical, emotional, financial and/or legal support if these needs are identified. Furthermore, they are able to arrange meetings between the patient/family and the clinical team if they have any questions about the care they received. Patient outcome data is routinely collected during the aftercare process. The Aftercare team will also facilitate the process for obtaining consent.

### Data management and confidentiality

Each patient will be given a unique study number as an identifier. Electronic data for analysis will not contain identifiable data and will be stored securely in password-protected files in a secure data environment. All paper files will be stored in locked cabinets in a restricted access office at EAAA study sites (Norwich and Cambridge). Data access will only be granted by the CI to authorised trial team members.

### Statistical methods

Descriptive statistics will be calculated to describe the processes and physiological endpoints, including technical, clinical, and safety endpoints. Computed statistics will be appropriate to the normality of the data and presented as proportions (±95% confidence intervals), means (±standard deviation) and medians (±interquartile range) as appropriate. Data will be processed and analysed using a combination of Excel (Microsoft, Redmond, WA, USA) and the R statistical programming language (R Studio, R Foundation for Statistical Computing, Vienna, Austria).

## Ethics and funding

### Research ethics approval

The London-Bromley REC has approved the trial (23/LO/0996). The trial is registered at ClinicalTrials.gov (NCT06071910).

### Patient and public involvement

The EAAA patient forum group were consulted during the development phase of the study. This is a diverse group of patients and relatives, including survivors of cardiac arrest, as well as patients treated for other conditions such as major trauma. A facilitated discussion was held on May 16, 2023 to gather views on the study proposal. Feedback from participants was considered in the design of the project. In particular, the patient forum strongly supported the study’s consent and information-sharing processes. The patient forum will continue to be consulted and updated on the trial during quarterly meetings, and the final results will be presented to the group following the conclusion of the trial.

### Patient consent

Patients eligible for the study will be in cardiac arrest and, therefore, unable to give consent to enter the study. Furthermore, given the time-critical nature of OHCA, there will not be sufficient time to consult the patient’s next-of-kin or a legally authorised consultee in order for them to make an informed decision about the patient’s involvement in the study. In England, the legal framework for conducting non-CTIMP trials in this context follows the Mental Capacity Act 2005 principles.^39^ Using this legal framework, precedent from previous trials of OHCA in England, and approval from the NHS Health Research Authority REC, the initial study enrolment will take place without consent.^39^, ^40^ Subsequent written informed consent will be sought from patients who regain capacity or a legally authorised consultee if the patient lacks capacity. Consent will only relate to continuation in the study and future follow-up, as the intervention will have already occurred. This subsequent informed consent process will run alongside routine contact and support from the EAAA Aftercare team. For patients who die before consent can be obtained, in a process agreed with the REC, the next-of-kin will receive a letter informing them that the patient was recruited into the study. This will also be followed up with routine contact from the EAAA Aftercare team, with a member of the research team additionally available to answer any questions related to the study.

### Research governance

A trial management committee (TMC) has been assembled to conduct the day-to-day administration of the study. The TMC consists of an independent chair and key members from the study team (CI, PI, study coordinator and data manager). The TMC will monitor all aspects of the conduct and progress of the trial, including adherence to the protocol, Good Clinical Practice; and reporting of any adverse events (AE) or serious adverse events (SAE) to the sponsor (Queen Mary University of London) and Research Ethics Committee (REC).

AEs are defined as any untoward medical occurrence in a participant to whom an intervention has been administered. SAEs are defined as any adverse event that is life-threatening, requires hospitalisation or prolongation of current hospitalisation or results in persistent or significant disability or incapacity. However, as this study recruits patients who are in refractory OHCA; untoward medical occurrences, death, prolonged hospitalisation, and disability are common, expected and often inevitable outcomes. Therefore, these events will not be recorded as AEs/SAEs unless considered to be ‘unexpected’ or directly related to the intervention.

A trial steering committee (TSC) has also been assembled with an independent chair, three independent experts in the field of adult resuscitation medicine, and a patient and public representative. The TSC will meet before patient recruitment, at 3-months and 6-months after the trial has started and then every 6-months thereafter. The TSC will make recommendations after considering the latest external evidence, safety, feasibility and any other arising issues.

Substantial amendments to the current protocol (v1.0, October 30, 2023) will only occur if approved by the REC. The protocol is available on the trial website: https://www.eaaa.org.uk/our-work/clinical-research/erica.

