**Methods:**

The Emergency Resuscitative Endovascular Balloon Occlusion of the Aorta in Out-of-Hospital Cardiac Arrest (ERICA-ARREST) study is a prospective, single-arm, interventional feasibility study. The trial will enrol 20 adult patients with non-traumatic OHCA. The primary objective is to assess the feasibility of performing Zone I (supra-coeliac) aortic occlusion in patients who remain in OHCA despite standard ALS in the UK prehospital setting. The trial’s secondary objectives are to describe the hemodynamic and physiological responses to aortic occlusion; to report key time intervals; and to document adverse events when performing REBOA in this context.

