### Trial design

This is a prospective, single-arm, interventional feasibility study, conforming to Stage 2A of the IDEAL clinical trial guidelines for evaluation of a surgical intervention.^36^ The study is designed to gather information on the feasibility of the intervention, so will not include a control group for comparison. During the study recruitment period, the EAAA team will continue to attend and manage patients in the East of England. In cases of OHCA, alongside standard resuscitation, the HEMS team will identify patients who meet study eligibility criteria (Table 2).

**Table 2 t0010:** Eligibility criteria for the ERICA-ARREST feasibility trial of prehospital Zone I (supra-coeliac) REBOA for refractory non-traumatic OHCA.

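### The adverse-event exemption is as broad as the adverse-event definition and decides what is recorded, so harms that resemble post-arrest illness and have no field in Table 3 may be under-recorded

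*Protocol article*

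**What the plan says.** The Methods paragraph of the abstract includes among the secondary objectives "to document adverse events when performing REBOA in this context".

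Research governance gives the definitions. For adverse events: "AEs are defined as any untoward medical occurrence in a participant to whom an intervention has been administered". For serious ones: "SAEs are defined as any adverse event that is life-threatening, requires hospitalisation or prolongation of current hospitalisation", with persistent or significant disability or incapacity as the remaining criterion. Death is not among the criteria.

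The same paragraph then says that in this population "untoward medical occurrences, death, prolonged hospitalisation, and disability are common, expected and often inevitable outcomes", and draws the consequence: "Therefore, these events will not be recorded as AEs/SAEs unless considered to be" unexpected "or directly related to the intervention".

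Table 1, which lists the outcome measures, covers device delivery, timings, haemodynamics, cerebral oximetry and end-tidal CO2. It contains no adverse-event or safety outcome. The Statistical methods section nevertheless includes safety endpoints among those to be summarised descriptively. On design, Trial design says the study is meant to inform on feasibility, "so will not include a control group for comparison".

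**The concern.** Keeping expected disease events out of expedited reporting is ordinary practice in emergency research. This rule goes further, because expectedness and relatedness decide whether an event is recorded as an adverse event at all. If such an event has no other data field, a later reader cannot revisit the attribution, and the steering committee, which is to consider safety, would not see the event as an adverse event.

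The harms most exposed are those that a period of aortic occlusion and a prolonged cardiac arrest could each explain. Without a comparison group, the judgement that such an event belongs to the arrest cannot be checked against a background rate. The results are meant to inform the design of later efficacy studies, so a safety count that depends on attribution would be carried into them.

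**Working it through.** The article states no event rate, safety threshold or derivation of the sample size, so there is no figure to reproduce. The check is mainly a comparison of texts.

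**Step 1. Definition against exemption.** The definition covers any untoward medical occurrence after the intervention. The exempted list opens with untoward medical occurrences, without qualification. The two classes coincide, so as worded any adverse event can fall under the exemption. The paragraph declares the whole class expected, which leaves direct relatedness as the main way back into the record.

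**Step 2. Serious-event definition against the exemption.** The definition omits death. The next sentence exempts death, which presupposes that it would otherwise count. The two sentences do not agree.

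**Step 3. What Table 3 captures whatever the rule says.**

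| Event | Listed field in Table 3 |
|---|---|
| Death | Yes: survival to discharge, survival to 30 days, time life pronounced extinct |
| Local haemorrhage, lower limb ischaemia, infection, aortic or femoral dissection, vessel injury, surgical repair | Yes, as examples of access-related complications |
| Visceral, renal or spinal ischaemia | None named |
| Device malposition or malfunction | None named |
| Disability | None |
| Prolonged hospitalisation | None |

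The complications field is itself limited to access-related events. Of the four classes named in the exemption, death is fully covered elsewhere, untoward occurrences are covered in part, and disability and prolonged hospitalisation are not covered.

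**Step 4. Objective against outcome list.** Documenting adverse events is a secondary objective and safety endpoints are to be summarised, but Table 1 has no such outcome.

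**Step 5. Illustration for a harm outside Table 3.** The only input from the document is n = 20, from Timescale: "The study will continue until 20 ERICA-ARREST patients have been enrolled, or 24 months have elapsed". Two inputs are assumptions: p, the true per-patient rate, and s, the share of events that pass the recording rule. Expected recorded events are 20 × p × s. The chance of recording at least one is 1 − (1 − p × s)^20.

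| p | s = 1 | s = 0.5 | s = 0.25 |
|---|---|---|---|
| 5% | 1.0 events; 0.64 | 0.5; 0.40 | 0.25; 0.22 |
| 10% | 2.0; 0.88 | 1.0; 0.64 | 0.5; 0.40 |
| 20% | 4.0; 0.99 | 2.0; 0.88 | 1.0; 0.64 |

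For example, with p = 10% and s = 0.5, 1 − 0.95^20 = 0.64. Each unrecorded event moves the observed rate by 1/20 = 5 percentage points. Even with full recording, 0 of 20 has an exact two-sided 95% upper limit of 1 − 0.025^(1/20) = 16.8%, so the study has little information on rare harms to spare.

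**The case against.** The strongest reply is that the rule is narrower than it looks and that the rest of the article fills most of the gap. The two exceptions are joined by or, so a directly related event is recorded even when it is expected. The exclusion is from being recorded as an adverse event, not from the dataset. Table 3 collects deaths and a substantial list of vascular complications for each patient. Each case has a structured debrief with the Chief Investigator within 24 hours, the management committee has an independent chair, and the steering committee is to consider safety. The full protocol and the case report form are not shown and may give an assessor, causality criteria or an expected-event list. The primary outcomes are unaffected.

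Most of this stands, and it rules out several stronger readings that a reader might draw:

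- That the study cannot document adverse events, or is bound to under-count harm. The relatedness exception and Table 3 show otherwise.
- That deaths or limb ischaemia could leave no trace. Both have listed fields.
- That the unblinded operator decides attribution. The operator completes the case report form, but the article does not say who judges expectedness or relatedness.

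The reply does not answer the breadth of the exemption, its use to govern recording, or the absence of listed fields for the remaining harms. These come from the published wording, not from what an article leaves out. A fuller document would have to narrow that wording, not merely add to it.

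**Conclusion.** The concern holds in a limited form. The exemption is worded as widely as the definition it qualifies and makes recording depend on attribution in an uncontrolled study. Followed as written, it may under-record non-access harms that resemble post-arrest illness and have no field in Table 3. The omission of death from the serious-event definition and the absence of a safety outcome from Table 1 are separate mismatches. The first is a drafting slip and does not remove deaths from the data.

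The size of any under-count cannot be computed, because the documents give neither an event rate nor the share of events that would be judged both expected and unrelated. The illustrative probabilities rest wholly on assumed p and s. They show how sensitive a 20-patient count is, not what will happen. The conclusion also assumes that the unseen case report form does not already record these events regardless of attribution.

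**What to change.** 1. Separate recording from reporting. Record a short pre-listed set of REBOA-relevant events for every enrolled patient, whatever their presumed cause. The set should include visceral, renal and spinal ischaemia, device malposition or malfunction, disability and prolonged hospitalisation, alongside the vascular and survival items already in Table 3.
2. Store relatedness and expectedness as separate fields, and let the exemption govern only onward or expedited reporting to the sponsor and ethics committee.
3. Add death as a criterion in the serious-event definition, so that it agrees with the sentence that follows.
4. Add adverse events to Table 1 as a secondary outcome, matching the objective in the abstract. Give counts both regardless of attribution and as attributed.

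The cost is an amendment to the protocol and case report form, slightly more data entry for at most 20 patients, and a harm rate that will look less favourable. Because the unfiltered count will include events caused by the arrest itself, both counts should be shown together.

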### Dissemination of findings

The trial results will be presented locally, regionally, and nationally at relevant academic conferences. A manuscript summarising the study’s findings will be written by the working group following completion for consideration of publication in a peer-reviewed medical journal.

## Conclusion

The ERICA-ARREST study will evaluate the feasibility of deploying REBOA in OHCA for the first time in a UK Helicopter Emergency Medical Service. Using compressed geography, and targeted dispatch, alongside a well-established femoral arterial access programme, the study will assess the feasibility of delivering the intervention in a mixed UK urban and rural setting, within a rapid timescale. The results of this trial will inform the design of future efficacy studies, which will investigate whether the implementation of REBOA can improve survival in OHCA patients who do not respond to standard ALS.
